## 1. Introduction

Caregivers have a low quality of life due to the patient worsening, challenges faced with the progression of the health condition, changes in the routine, and reduction in leisure activities (Diniz et al., 2018; Alves et al., 2019; Nogueira et al., 2019; Sanches Slusarski Martins et al., 2022). Although the low quality of life and increased burden of caregivers are well-established characteristics in literature, this topic still requires greater visibility and attention to propose interventions (Burke et al., 2017; Sandstedt et al., 2018).

Informal caregivers (i.e., unpaid individuals who help patients in activities of daily living and medical programming) may also experience issues in family relationships and economic difficulties and suffer from social stigma and physical burden (Ploeg et al., 2017). Approximately 70 to 80% of caregivers are informal; among these, 30 to 68% have anxiety or depression (Wilz and Kalytta, 2008). In addition, the strain increases the risk of cardiovascular diseases and mortality by 23 and 63%, respectively (Richard and Scott, 1999).

Individuals with amyotrophic lateral sclerosis (ALS) present progressive muscle weakness, fatigue, and reduced mobility and functional activities (Lui and Byl, 2009). Moreover, a multidisciplinary team treats ALS focusing on symptoms (Ferreira et al., 2016) since this disease progression cannot be reversed or changed, requiring intermittent care. Informal caregivers are essential to support this population due to the intensive and complex care required (D'Alvano et al., 2022; Poppe et al., 2022). Schischlevskij et al. (2021) found that the functional status and disease severity of individuals with ALS were the main factors influencing caregiver burden. Moreover, cognitive changes (e.g., impaired attention, focus, and memory) and behavioral changes (e.g., irritability, frustration, impatience, and social isolation) in caregivers of individuals with ALS (Burke et al., 2015; Beeldman et al., 2016) and the need to learn how to manage assisted ventilation and enteral feeding has been involved in caregiver burden (Siciliano et al., 2017; Chu and Oh, 2020).

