### 2.3. Power calculation

Sample size was estimated using an online calculator (Dean, 2007) based on caregiver burden (primary outcome), which was evaluated using the Zarit scale. Moreover, the effect size was calculated based on post-training data from Duran Parra et al. (2019) (mean of 16 ± 9.9 and 31.4 ± 14.9 points for experimental and control groups, respectively), with a mean difference of 15.4 between groups. Thus, 22 participants (11 per group) were estimated, and the total sample was determined as 26 participants (13 per group), considering a dropout rate of 20%.

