### 2.14. Statistical analysis

Data will be analyzed using the Statistical Package for the Social Sciences software version 22.0 (IBM Corp., Chicago, IL, USA). Data will be initially characterized using descriptive analysis, and the significance level will be set at 5%. The Shapiro-Wilk test will be applied to verify data normality. Differences between groups on different evaluation periods will be analyzed using linear mixed models. The Bonferroni *post hoc* may be used for statistically significant results to identify specific differences. Moreover, an intention-to-treat analysis will be used to compare the groups by including all participants as allocated after randomization, ensuring an unbiased approach. Participants' data will be analyzed based on their intervention group, regardless of any dropouts. Values from the previous evaluation will be replicated and attributed to missing data due to dropout.

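### Carrying the previous score forward for dropouts shrinks the burden effect and is unnecessary beside the linear mixed model already named

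*Protocol article*

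**What the plan says.** Section 2.14 makes three statements that bear on missing outcomes.

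- The between-group analysis: "Differences between groups on different evaluation periods will be analyzed using linear mixed models".
- The analysis set: "an intention-to-treat analysis will be used to compare the groups by including all participants as allocated after randomization, ensuring an unbiased approach".
- The rule for missing values: "Values from the previous evaluation will be replicated and attributed to missing data due to dropout".

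The last is the only missing-data method in the article. There are three evaluations: baseline, after the six-week programme (revaluation 1) and 30 days later (revaluation 2). A participant lost before revaluation 1 would therefore have the baseline score entered as the post-programme score. One lost between the two revaluations would have the week-six score entered as the 30-day score. Section 2.3 plans for 20% dropout, which is about 5 of 26 participants (0.2 × 26 = 5.2).

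**The concern.** Carry-forward treats burden as frozen from the moment of dropout. The Introduction gives reason to doubt this: it reports that "the functional status and disease severity of individuals with ALS were the main factors influencing caregiver burden", and describes the disease as one whose course cannot be reversed. Burden may also fall, since both arms receive the self-care booklet. Whenever scores change for any reason, a carried value is a poor stand-in for the missing one.

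At stake is the estimate for a primary outcome in a 26-person trial. A dropout before revaluation 1 contributes no treatment effect at all, so a real effect is diluted. At revaluation 2, persistence is assumed for those lost after week six instead of being measured. The step is also not needed to keep all randomised participants in the analysis, because the named model does that with the observed data.

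**Working it through.** **Inputs from the protocol (section 2.3).** Planning data: "mean of 16 ± 9.9 and 31.4 ± 14.9 points for experimental and control groups, respectively", "with a mean difference of 15.4 between groups"; 11 per group evaluable, 13 per group recruited, 20% dropout.

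**Assumed, because the article does not give them.** Two-sided 5% test; 80% power; baseline-to-follow-up correlation 0.6 (0.5 as a check); all dropout before revaluation 1; the split of dropout by arm; any drift in burden.

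**1. The plan's own figure.** Pooled SD = √((9.9² + 14.9²)/2) = √160.01 = 12.65. Then n per group = 2 × (1.960 + 0.842)² × 12.65² / 15.4² = 10.6, so 11 per group and 22 in total, as stated. Adding 20% gives 22 × 1.2 = 26.4, stated as 26.

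**2. Expected difference under carry-forward.** With dropout proportion d in an arm, the expected arm mean is (1 − d) × post mean + d × baseline mean. With equal d and a common baseline mean, the baseline terms cancel:

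- d = 10%: 0.9 × 15.4 = 13.9
- d = 20%: 0.8 × 15.4 = 12.3
- d = 30%: 0.7 × 15.4 = 10.8

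**3. Coverage and power at revaluation 1.** Simulation with 13 per arm, SD 12.65, correlation 0.6 and 20% dropout per arm. The baseline-adjusted comparison of observed data stands in for the mixed model.

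| Analysis | Estimate | 95% CI coverage | Power |
|---|---|---|---|
| Carry-forward | 12.3 | about 89% | 83% |
| Observed data | 15.3 | 95% | 88% |

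With correlation 0.5, power is 78% against 83%. If dropout also depends on the baseline score, it is 75% against 82%, with carry-forward coverage 89%.

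**4. Source of the coverage loss.** The carry-forward model standard error is 4.06 and the true sampling SD of the estimate is 4.07, so the error is not understated for the quantity being estimated. The bias is 15.4 − 12.3 = 3.1 points, or 3.1/4.06 = 0.76 standard errors. That displacement explains the undercoverage.

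**5. No true effect.** With equal dropout the formula gives zero bias, and simulated type I error is about 5%. With unequal dropout and a common drift, the spurious difference is drift × (difference in dropout):

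- Worsening of 4 points, EG 30% and CG 10%: 4 × 0.2 = 0.8 points in favour of EG (type I error about 6%).
- Worsening of 6 points, EG 40% and CG 10%: 6 × 0.3 = 1.8 points in favour of EG (type I error about 8%).
- Improvement of 8 points, EG 30% and CG 10%: 8 × 0.2 = 1.6 points against EG. The simulation, with dropout depending on baseline, gave about 2.0 and type I error 7.7%.

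**6. True effect with unequal dropout.** With a common baseline of 31.4 and no change in CG, EG 30% and CG 10% gives (0.9 × 31.4 + 0.1 × 31.4) − (0.7 × 16 + 0.3 × 31.4) = 31.4 − 20.62 = 10.8. With EG 10% and CG 30% it is 31.4 − (0.9 × 16 + 0.1 × 31.4) = 31.4 − 17.54 = 13.9.

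**The case against.** The strongest reply is that, at the plan's own dropout rate, carry-forward is conservative and the loss modest. The estimate moves toward no difference, power falls by about five percentage points, and type I error stays at 5% when dropout is equal. This stands, and it limits how serious the point is. It does not rescue the rule: an interval with 89% coverage is not a 95% interval, and conservatism is not assured once dropout differs between arms.

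A reader might infer several stronger things that the document does not support.

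- *That carry-forward will manufacture a benefit for EG.* This needs worsening burden and heavier loss in EG. The article gives neither a rate of Zarit change over six weeks nor dropout by arm. If burden improves, the bias reverses.
- *That the standard errors are falsely small because filled values count as data.* They are about 11% smaller than with observed data only (4.05 against 4.55), but they match the sampling variability of the diluted estimate at revaluation 1.
- *That durability at revaluation 2 is overstated.* This is so only if the effect wanes after week six, which the article does not say.
- *That the absence of a missing-data sensitivity analysis is a defect.* It may sit in an analysis plan that is not shown.
- *That participants who stop will not be assessed.* Section 2.11 provides for remote reassessment of all participants, and section 2.13 for reminders of evaluations.

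Two limits of the check also stand. It covers revaluation 1 with a baseline-adjusted comparison, not the full three-evaluation mixed model. And that the filled values enter the mixed model is inferred, although section 2.14 names no other between-group analysis.

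**Conclusion.** The point holds as a should-fix. Section 2.14 states a carry-forward rule that its own model makes unnecessary. At the protocol's 15.4-point difference and 20% dropout per arm, the rule costs about 3 points of expected effect, about 6 percentage points of interval coverage and about 5 of power. The dilution needs only the protocol's figures, dropout before revaluation 1, equal dropout and a common baseline mean. The coverage and power figures also rest on the assumed correlation of 0.6. Dropout after revaluation 1 would not dilute the revaluation 1 result.

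The direction is toward no difference under equal dropout with a real effect, nil under equal dropout with no effect, and unpredictable when dropout is unequal and scores drift. The spurious differences of 0.8 to 1.8 points are illustrations under assumed conditions. Either way, the section's assurance of an unbiased comparison is not met by the rule that follows it.

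**What to change.** Delete the carry-forward sentence from section 2.14. Replace it with a statement that the linear mixed model will be fitted by REML to all observed values of all randomised participants, in the arm to which they were allocated, with no imputation, and that this is valid under missing-at-random. Drop the assurance of unbiasedness or make it conditional on that assumption. Carry-forward or a delta-shift analysis may be kept as an optional sensitivity check.

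The change costs a few lines of wording. It needs no further participants or data and leaves the sample size as it is. The downside is a somewhat wider standard error, about 4.55 instead of 4.05 points in the scenario above, in exchange for an estimate centred on the true difference under missing-at-random.

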## 3. Discussion

This is the first study comparing a synchronous (follow-up via video call) and asynchronous (follow-up via messages and informative booklet) multidisciplinary self-care educational program for caregivers of individuals with ALS. According to Chi and Demiris (2015), caregivers approve and feel comfortable using telerehabilitation to improve self-care and quality of life. In this sense, telerehabilitation has been growing in the healthcare field and can be a useful tool to promote physical activities and self-care.

Despite being aware of the benefits of physical activity, caregivers face barriers, such as lack of support from family members, self-motivation, and time to perform self-care activities, guilty feelings, and stress (Farran et al., 2008; Marquez et al., 2012; Martin and Keats, 2014). Most caregivers have reported difficulty performing self-care activities because they prioritize patient care (Son et al., 2007; Farran et al., 2008; Snyder and Vitaliano, 2020). In this sense, these barriers will be addressed in this multidisciplinary study, highlighting the need for interventions involving different professionals (e.g., psychologists, and nutritionists) for the biopsychosocial management of caregivers. Telerehabilitation aims to facilitate adherence to this program.

In this study, all participants will receive the informative booklet on health and self-care from a multidisciplinary team, allowing easy access to this information. This study aims to understand whether monitoring and providing synchronous information result in better outcomes than asynchronous information. It may contribute to the knowledge about the applicability of telerehabilitation for caregivers of individuals with ALS and reinforce the need for self-care.

This study has limitations, such as the possible sociodemographic homogeneity of caregivers, considering that they will be recruited in the same region. Caregivers will read the informative booklet and perform the physical activity individually and spontaneously throughout the days of the week due to their routines. Although this self-applied intervention may present low reliability, the *Sênior Saúde Móvel* platform will allow greater accuracy of the level of physical activity. The exercise guidelines are not based on the specific needs and characteristics of caregivers and may not have good applicability for all; however, caregivers will be asked to report on possible limitations and difficulties in performing some exercises, which may be adapted through professional guidance. In addition, the EG will receive the interventions via group video calls. In this sense, the follow-up of the groups might be difficult throughout the weeks due to different caregivers' demands, hampering the evaluation of the effect of the intervention in groups.

To solve the mentioned limitations, caregivers will receive detailed information regarding the booklet and be able to solve any doubt at the first evaluation. A team will be available to support the caregivers in performing the exercises and applying the booklet in their daily routines during the program via WhatsApp groups. The *Senior Saúde Móvel* platform will be used for remote data collection to ensure reliability in evaluating the proposed program, allowing identification and monitor the adherence and execution of the program.

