**Methods:**

This single-blinded randomized clinical trial will recruit 26 caregivers and randomly allocate them to the experimental (EG = 13) or control group (CG = 13). The EG will receive an informative booklet and participate in a 6-week synchronous telerehabilitation program with a neuropsychologist, nutritionist, and physiotherapist to discuss physical and mental health. The CG will receive an informative booklet on self-care and physical activity and weekly phone calls for 6 weeks to solve questions about the booklet. Outcomes will include the caregiver burden (Zarit scale), quality of life (World Health Organization Quality of Life BREF), pain (McGill Pain Questionnaire), stress (Perceived Stress Scale), and depression (Beck Depression Inventory), which will be evaluated at the baseline after the six-week program and 30 days after the program. Additionally, we will assess daily the nocturnal awakenings, sleep patterns, level of physical activity, and heart rate variability.

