Weight loss in ALS has been associated with reduced survival; thus, healthcare professionals must establish maintaining body weight as a therapeutic goal (Ning et al., 2019; van Mantgem et al., 2020). In this sense, caregivers' knowledge and influence on nutritional behaviors are essential to increase caloric intake and body weight in individuals with ALS (Genton et al., 2011; Marin et al., 2011; Coates et al., 2023). Thus, a support network should be implemented to help with nutritional issues in this disease (Ludolph et al., 2020).

The implementation of physical activity in the routine of caregivers has been associated with reduced stress and improved quality of life and wellbeing (Lambert et al., 2016). However, caregiving demands hamper the adherence to face-to-face programs due to the limited time available, the need for travel, and difficulty finding someone to care for the patient (Winter and Gitlin, 2007). Thus, remote self-care activities are faster and more practical than face-to-face and may be preferred (Hearn et al., 2019) since caregivers can participate in meetings and receive professional guidance and information via video conferences (Van Egmond et al., 2018).

The self-care concept comprises actions to ensure self-health and wellbeing (Lobo et al., 2023). In this sense, caregivers of individuals with ALS need to recognize the importance of self-care since they face great physical and emotional challenges (Young et al., 2023). Moreover, caregivers can maintain their health and quality of life by prioritizing self-care, which improves their ability to care for the patient adequately and efficiently (D'Alvano et al., 2022).

Telerehabilitation is defined as remote rehabilitation via communication technologies that different health professionals can use (e.g., physical, occupational, and speech therapists and psychologists). This tool can be combined with evaluation, monitoring, and health education, may reduce travel costs, and allow flexible schedules and integration into the routine of users (Van Egmond et al., 2018). Moreover, telerehabilitation can be implemented asynchronously (i.e., without real-time contact) or synchronously (i.e., real-time video and audio) using video conferences with one or more individuals simultaneously (Kern, 2006).

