Previous studies (Cottrell et al., 2017; Grona et al., 2018; Jiang et al., 2018; Bettger et al., 2020; Prvu Bettger and Resnik, 2020; Yeroushalmi et al., 2020) have shown that telerehabilitation may reduce pain and recover motor function in individuals with musculoskeletal dysfunctions. Moreover, it decreases healthcare costs and improves treatment adherence, physical and mental function, and quality of life (Barlow et al., 2009; Vloothuis et al., 2019).

Educational programs can provide information to cope with the challenges of caregiving and implement relevant topics based on self-care (e.g., sleep health, healthy eating, mental health practices, and physical exercises to support the caregivers' quality of life), allowing informal caregivers to have confidence in providing care and focus on their physical and mental wellbeing (González-Fraile et al., 2021; Zarotti et al., 2021). However, the effects of telerehabilitation on informal caregivers of individuals with ALS are unclear (Watermeyer et al., 2015; Galvin et al., 2018; Burke et al., 2019) since the needs and circumstances may vary for each caregiver and the patient and due to different training programs and telerehabilitation limitations. Moreover, a lack of studies regarding the long-term effects of continuous remote evaluation and telerehabilitation and its efficacy in different disease stages has been observed, hampering to generalize of the studied effects.

In this sense, the following question emerged: Does the quality of life, depression, burden, and stress of caregivers receiving a synchronous telerehabilitation program improve compared with those assisted individually and asynchronously? Thus, we hypothesized that a synchronous telerehabilitation program might reduce the burden, stress, pain, and depression and improve the quality of life of caregivers of individuals with ALS, enhancing their mental and physical health. The benefits may include reduced social isolation and improved access to support and guidance services, coping strategies for stress and emotional burden, and knowledge regarding ALS and adequate care strategies.

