This study aimed to design a randomized clinical trial protocol to evaluate the impact of a self-care education program via synchronous telerehabilitation on the quality of life and burden of caregivers of individuals with ALS. All the content addressed in both intervention proposals is innovative, as planned by a multidisciplinary team, aiming to consider different aspects that influence the quality of life, depression, burden, pain, and stress of caregivers. Additionally, the present study will use wearable technologies as a way to monitor and assess physiological states remotely, such as nocturnal awakenings, sleep patterns, level of physical activity, and heart rate variability. Results may show whether remote and synchronous programs favor the self-care of caregivers by improving time and access to health education.

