#### 2.8.2. Control group

A physiotherapist will also visit the participants in the CG to evaluate their health condition, deliver the informative booklet, and instruct them on the importance of reading and using the booklet (Appendix 1). Next, trained researchers will contact the participants via phone calls during the 2nd to 6th week of the intervention to verify their physical and mental health and collect information on completing physical exercises and habits proposed in the booklet. The researcher should record any relevant information. Figure 2 shows the questions for participants. After the intervention period, a new visit will be performed for revaluation.

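### The trial can compare two support packages, but it cannot attribute a difference to synchronous versus asynchronous delivery, because the controls also have live phone contact and the arms differ in other ways

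*Protocol article*

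**What the plan says.** **The question.** The research question in section 1 (Introduction) asks whether "caregivers receiving a synchronous telerehabilitation program improve compared with those assisted individually and asynchronously". Section 3 (Discussion) calls the study the first "comparing a synchronous (follow-up via video call) and asynchronous (follow-up via messages and informative booklet) multidisciplinary self-care educational program" and adds: "This study aims to understand whether monitoring and providing synchronous information result in better outcomes than asynchronous information".

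**The broader aim.** The last paragraph of section 1 states a different aim, which is to "evaluate the impact of a self-care education program via synchronous telerehabilitation on the quality of life and burden of caregivers". The Abstract's Introduction is worded in a similar way.

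**The definition.** Section 1 says that telerehabilitation can be delivered "asynchronously (i.e., without real-time contact"), or synchronously, meaning live sound and picture.

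**The control contact.** The Abstract (Methods) gives controls "weekly phone calls for 6 weeks to solve questions about the booklet". Section 2.8.2 says that "trained researchers will contact the participants via phone calls during the 2nd to 6th week of the intervention", to check health and ask about the booklet's exercises and habits. Section 2.12 (Adverse events) refers to weekly contact by video or phone during the intervention, with messages and the booklet as the route at other times. The Discussion mentions only messages and the booklet as the control follow-up.

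**The experimental contact.** Section 2.8.1 describes weekly online meetings over 6 weeks, in subgroups of three to five, led by a physiotherapist, a psychologist and a nutritionist, on set topics.

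**The concern.** The label on the comparison does not match the arms as described. If the control arm has live calls, it is not asynchronous in the protocol's own terms. A positive result could then not be read as live contact beating no live contact.

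Even with a loose reading of the label, delivery mode changes together with the provider, the format and what is taught live. Contact with peers in a group, or with a psychologist, could plausibly affect burden and quality of life whether or not the contact is synchronous.

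What is at stake is the sentence the trial may print as its conclusion. The Discussion already announces a delivery-mode inference, and its limitations paragraph mentions the difficulty of following groups but not this confounding.

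**Working it through.** The plan gives no figure on this point, so the check sets the passages side by side. The sample-size calculation in section 2.3 does not bear on it.

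**Step 1: is the control arm asynchronous by the protocol's definition?**
- The definition in section 1 requires that there be no real-time contact.
- The Abstract and section 2.8.2 both give controls phone calls, and section 2.12 is consistent with this.
- A phone call is real-time contact, so the condition fails.
- A call without picture does not clearly meet the synchronous definition either. The two categories leave it unclassified, but it is not asynchronous.

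**Step 2: do the accounts of control contact agree?**

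| Place | Control follow-up |
|---|---|
| Abstract, Methods | Weekly calls for 6 weeks, answering booklet questions: 6 calls |
| Section 2.8.2 | Calls in weeks 2 to 6, checking health and booklet use: 6 − 2 + 1 = 5 calls if weekly |
| Section 3 | Messages and booklet; calls not mentioned |

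The first two differ by one call and in stated purpose. The third leaves out the main live component of the other two.

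**Step 3: what else differs between the arms?**

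| Component | Experimental | Control |
|---|---|---|
| Booklet | Yes | Yes |
| Physiotherapist visit | Yes | Yes |
| Live channel | Online meeting | Phone call |
| Provider of weekly contact | Three health professions | Trained researchers |
| Format | Subgroups of three to five | Individual (research question, section 1) |
| Live content | Set topics, taught | Check questions; booklet queries (Abstract) |

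The written content is shared, so content differs only in the live contact.

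**Step 4: what can two arms identify?** Suppose, for simplicity, that the effects add up:

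Difference between arms = channel + provider + format + taught live content.

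Two randomised arms estimate the left-hand side. That is one equation with four unknowns, and interactions would add more. The total is identified and unbiased for the package contrast. No single term is identified, and no analysis of these two arms changes that. Even if the last three terms were zero, the channel term would compare a live online meeting with a live phone call, not live contact with its absence.

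**The case against.** The strongest reply is that a multicomponent programme tested against an active control is a legitimate design, and that the aim at the end of section 1 already states it that way. This stands: the trial answers that aim. The research question also openly says that controls are assisted individually, so the format difference is declared. Neither point covers the Discussion, which frames the contrast as delivery mode alone, or the provider and live-content differences.

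It can also be said that the control education comes through the booklet and is asynchronous in that sense, while the calls only monitor. Section 2.8.2 fits this, but the Abstract has the calls answering questions about the booklet. Nor does the Discussion say that messages are the only follow-up. Section 2.12 shows that messages and calls can coexist, so its wording is incomplete rather than flatly exclusive.

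A reader might infer more than the text supports:
- **A gap in contact time.** Meeting length is given, but call length is not, so the gap is unknown.
- **Contamination.** The Discussion offers team support "during the program via WhatsApp groups" without naming an arm. It does not say that arms share a group, and an article may leave that detail to the full protocol.
- **That the effectiveness claim for telerehabilitation must go.** The experimental programme is telerehabilitation, tested against booklet plus calls. The claim can stand if it is read relative to that comparator.

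**Conclusion.** The point holds for the delivery-mode inference only. By the protocol's own definition the control arm is not asynchronous, and at least three further components (provider, format, taught live content) vary with the label. The share of any observed effect due to synchronous delivery is not identifiable, and the documents give no basis for a numerical range.

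A reader might go further and conclude that the randomised comparison is invalid. The documents do not support that. The package contrast is intact, and nothing here alters allocation, outcomes, sample size or analysis.

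The conclusion assumes that the phone calls in the Abstract and section 2.8.2 are live conversations, as their stated purposes imply, and that the figures and appendix not shown do not redefine control contact. This should be changed before results are reported, because it governs what the trial may conclude.

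**What to change.** 1. Reword the research question in section 1, and the aim and intended conclusion in section 3, as booklet plus multidisciplinary group video programme versus booklet plus individual phone follow-up. This matches the aim already stated at the end of section 1.
2. Drop the inference that synchronous information is better or worse than asynchronous information.
3. Add to the limitations in section 3 that provider, group format and taught live content differ along with the channel, so their effects cannot be separated.
4. Reconcile the Abstract, section 2.8.2 and section 3 to one description of control contact: channel, weeks and purpose. The investigators must say which schedule applies.

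The cost is a few sentences and a narrower claim. No data collection or analysis changes.
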